### Penetration aspiration scale score (incl. definitions):

11.1

The PAS is a validated 8-point ordinal scale that quantifies penetration and aspiration events observed during instrumental swallow assessment.^[38]^ The scale ranges from 1 (normal swallow: material does not enter airway) to 8 (severe aspiration: material enters the airway, passes below the vocal folds & no effort is made to eject). Swallowing severity will be assessed using the PAS observed during FEES at screening and on day 2 (approx. 24–60 hours) after completion of the final PES treatment. The worst PAS score for each thin liquid bolus will be recorded in the eCRF. IFRC PAS scores will be entered in a separate portion of the eCRF.

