### Dysphagia outcome and severity scale (DOSS)

11.3

The DOSS is a simple, easy-to-use, 7-point scale developed to systematically rate the functional severity of dysphagia based on objective assessment and make recommendations for diet level, independence level, and type of nutrition.^[40]^ The score ranges from 1 (severe dysphagia) to 7 (normal in all situations). DOSS scores will be recorded in the eCRF at the screening, day 2, 7 ± 1 days and 14 ± 1 days visits.

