### Statistical hypotheses

17.1

The primary effectiveness analysis (Finkelstein-Schoenfeld (FS)^[32]^ (win-ratio) statistic) is on the composite of two endpoints in the following hierarchy based on clinical priorities:

1.Swallowing safety based on worst PAS score in series of up to 4 boli using thin stimuli (water) for each patient as determined by a FEES assessment on day 2 (approx. 24–60 hours) after completion of the final PES treatment, converted to a trichotomized ordinal response of safe (PAS 1–3), penetration (PAS 4–5), or aspiration (PAS 6–8).2.DOSS score determined by bedside assessment 7 ± 1 days after completion of the final PES treatment.

Using the FS approach, each treatment arm patient will be compared to each control arm patient and a winner/loser determined. Comparisons are made hierarchically as defined above so that if the treatment arm patient performs better than the control arm patient with respect to the first hierarchy level (PAS) outcome then the treatment arm patient gets a score of +1 (winner) otherwise a score of −1 (loser) is assigned. If the first hierarchy level comparison is tied then the comparison is done with respect to the second outcome (DOSS) and the same scoring procedure is followed. The FS-statistic is based on the mean of the scores obtained from all such comparisons. If P is the probability that a randomly picked treatment arm patient performs better than a randomly picked control arm patient, then the expected value of the FS-statistic is given by 2 (P – 0.5). The hypothesis of interest is a one-sided null: H_0_: *P* ≤ .5 vs the one-sided alternative H_1_: *P* > .5. PAS and DOSS scores are ordinal outcomes. For each pair of patients evaluated (a pair being composed of one treated patient and one control patient), a binary outcome is derived that indicates whether the treated patient or the control patient performs better.

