### Sample size determination

17.2

Sample size calculations were carried out using simulations and are adjusted for interim analysis. Assuming that 50% of control patients will move from PAS score of 6–8 at baseline to a PAS score of 1–5 post-intervention and the corresponding number of patients in the PES treatment group is 65% (15% effect-size) and that the PES treatment group will benefit with a mean increase of 0.7 points on the DOSS score, 100 patients per arm will be required to achieve a power of at least 90%. Thus N_planned_ = 200 is the minimum sample size (unless the study is stopped early for futility at the only interim analysis). To allow for adaptations in design with respect to sample size and population enrichment, a maximum (evaluable) sample of N_max_ = 360 is pre-specified. To account for a 10% lost-to-follow-up, a maximum of 400 patients will be recruited.

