### Statistical analyses

17.4

Tabulations will be produced for appropriate demographic, baseline, effectiveness and safety parameters. For categorical variables, summary tabulations of the number and percentage within each category (with a category for missing data) of the parameter will be presented. For continuous variables, the mean, median, standard deviation, minimum and maximum values will be presented. Time to event data will be summarized using Kaplan–Meier methodology using 25th, 50th (median), and 75th percentiles with associated 2-sided 95% confidence intervals, as well as percent of censored observations. Formal statistical hypothesis testing will be conducted at the 1-sided, 0.025 level of significance. A Statistical Analysis Plan (SAP) will detail all statistical analyses planned for this study and will be established prior to the planned Interim Analysis.

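### The primary Finkelstein-Schoenfeld test, as written, makes no use of baseline DOSS; the test is valid, but prespecified adjustment could add precision at little cost

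*Protocol article*

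**What the plan says.** Section 17.1 sets out the primary test. Under the FS approach "each treatment arm patient will be compared to each control arm patient and a winner/loser determined", first on the three-category PAS from the day-2 FEES and, if tied, on DOSS at day 7 ± 1. The statistic is the mean of the pairwise scores. The section mentions neither a baseline covariate nor stratified pairing.

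Both scales are also measured before treatment. Section 11.3: "DOSS scores will be recorded in the eCRF at the screening, day 2, 7 ± 1 days and 14 ± 1 days visits". Section 11.1: "Swallowing severity will be assessed using the PAS observed during FEES at screening", and again on day 2. Section 6.2 uses baseline DOSS in a secondary endpoint on change over time.

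Sections 3.1 and 5 require PAS of at least 6 for entry; no DOSS level is required. Section 8 stratifies randomisation by site and by neurological versus non-neurological admission. Section 17.4 leaves the detail of all analyses to a SAP that is to be in place before the interim analysis and is not shown.

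**The concern.** Day-7 DOSS decides every pair that ties on PAS, and baseline DOSS is an earlier reading of the same scale. If the two are correlated, part of the variation in the patients' win scores is predictable before randomisation, and the all-pairs mean leaves it in the error term. Neither the stratification nor the test as written deals with chance imbalance in baseline DOSS. At stake is power at a fixed sample size, or equivalently the number of patients needed for a given power. Section 18 itself expects recruitment to be limited by the expertise that FEES and PES require.

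**Working it through.** **Inputs from the article**
- Test level (17.4): "Formal statistical hypothesis testing will be conducted at the 1-sided, 0.025 level of significance", so z = 1.96.
- Sample size (17.2): "100 patients per arm will be required to achieve a power of at least 90" per cent.
- PAS effect (17.2): "50% of control patients will move from PAS score of 6–8 at baseline" to 1–5, against 65% on PES.
- DOSS effect (17.2): "mean increase of 0.7 points on the DOSS score".

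**Not given, so assumed over a range:** the DOSS SD, the PAS–DOSS correlation, the three-way PAS split, the interim rule and the baseline–outcome correlation r.

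**1. The plan's own figure.** The 90% cannot be reproduced uniquely, because the inputs just listed are missing, but it is attainable. The FS test was simulated with PAS first and then DOSS, permutation variance, one-sided 0.025, 100 per arm and no interim.
- With DOSS SD 1.0–2.0, PAS–DOSS correlation 0–0.7 and three PAS splits, power runs from 66% to 99%.
- With SD 1.25–1.5, correlation 0–0.5 and a 15-point gain in the safe category, it is 88–96%.
- The PAS dichotomy alone (50% vs 65%) gives 57% at 100 per arm and would need 227 per arm for 90%. The stated power therefore relies heavily on DOSS.

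**2. Gain by formula.** Let r be the correlation of the baseline covariate with the patient's FS score. Adjustment multiplies the variance by (1 − r²), so

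power = Φ[(1.2816 + 1.96)/√(1 − r²) − 1.96], starting from 90%.

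The equivalent increase in patients is 1/(1 − r²) − 1.

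| r | variance reduction | power | equivalent extra patients |
|---|---|---|---|
| 0.1 | 1% | 90.3% | 1% |
| 0.2 | 4% | 91.1% | 4% |
| 0.3 | 9% | 92.5% | 10% |
| 0.4 | 16% | 94.3% | 19% |
| 0.5 | 25% | 96.3% | 33% |

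For r = 0.5: 3.2416/0.8660 = 3.743; 3.743 − 1.96 = 1.783; Φ(1.783) = 0.963.

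**3. Gain by simulation.** The FS scores were residualised on a discretised baseline DOSS. Assumptions: DOSS SD 1.5, PAS–DOSS correlation 0.3, safe category 25% vs 40%, 100 per arm, 6,000 replicates. Here r is the correlation of baseline with each latent outcome.

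| r | unadjusted | adjusted | gain (points) |
|---|---|---|---|
| 0 | 89.0% | 89.0% | 0 |
| 0.1 | 89.0% | 89.2% | 0.2 |
| 0.2 | 89.2% | 90.2% | 1.0 |
| 0.3 | 89.2% | 91.8% | 2.6 |
| 0.4 | 89.9% | 94.6% | 4.7 |
| 0.5 | 89.6% | 96.4% | 6.7 |

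Gains are taken before rounding. Type I error of the adjusted test was 0.024 at r = 0, 0.024 at r = 0.3 and 0.023 at r = 0.5.

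If unadjusted power is lower, the gain is larger. With SD 1.75 and PAS–DOSS correlation 0.5, power goes from 83.3% to 86.7% at r = 0.3 and from 83.5% to 92.1% at r = 0.5.

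**4. In patients.** The adjusted test matches the unadjusted test at 100 per arm with about 90–95 per arm at r = 0.3 and about 75 at r = 0.5. This agrees with 100 × (1 − r²) = 91 and 75.

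**5. Which covariate.** Every randomised patient starts at PAS 6–8, which is a single category of the trichotomised endpoint. Only the 6/7/8 distinction is left to predict anything, so DOSS is the main candidate.

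**The case against.** The strongest reply is that nothing here is wrong. The article condenses a longer protocol, covariate adjustment is commonly settled in the SAP, and Section 17.1 describes how pairs are scored without ruling adjustment out. The test is valid and was sized by simulation for at least 90% power. The article does not show that baseline DOSS predicts outcome, and DOSS may itself vary little among confirmed aspirators soon after extubation. Changing the statistic also has consequences. The interim analysis carries stopping, sample-size re-estimation and enrichment rules (Section 15). Six or more sites by two admission groups make at least 12 strata, or about 200/12 ≈ 17 patients each, with some probably sparser.

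Most of this stands, and it limits the point. A reader might infer that the primary test is biased or underpowered, or that power is certainly being given away. The documents support neither: the test is sound, and at r of 0.1 or less the gain is about zero. Nor can one infer that the SAP lacks an adjusted analysis, since it is not shown, or that baseline PAS is a strong covariate, given its restricted range.

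The reply does not remove the recommendation. Section 17.1 already states the pairing rule and the statistic, so a SAP that simply follows it would be unadjusted. If baseline DOSS turns out to be uninformative, adjustment loses essentially nothing (89.0% either way at r = 0).

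**Conclusion.** The point holds as an efficiency recommendation. It is not an error or a contradiction. As written, the primary FS test uses no baseline information although baseline DOSS is on file for every patient, so precision may be lost.

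From a 90% base, the gain from adjustment is about 0 points of power at r ≤ 0.1, 1 at r = 0.2, 2–3 at r = 0.3 and 6–7 at r = 0.5. For r = 0.2–0.5 that is a 4–25% variance reduction, worth about 4–33% more patients, with type I error preserved. These figures rest on an assumed r and, in the simulation, on an assumed DOSS SD, PAS–DOSS correlation and PAS split, with no interim look.

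**What to change.** Prespecify in the SAP, before the interim analysis, a covariate-adjusted FS test as the primary analysis:
- Compute each patient's net win score from the hierarchy as already defined.
- Apply randomisation-based nonparametric covariance adjustment for baseline DOSS. Baseline PAS (6/7/8) is optional, because of its restricted range.
- Stratify by admission reason. If site is used as well, pool small sites by a stated rule.
- Use the same statistic at the interim and final analyses, and re-check the design simulations with it.
- Report the unadjusted FS result as a sensitivity analysis.

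No new data are needed. The cost is a short SAP passage, a little more programming and a re-run of the design simulations, including the interim rules.

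### The primary pair score has no value for pairs tied on both PAS category and DOSS, so the printed scoring rule, null hypothesis and binary-outcome statement do not fit together

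*Protocol article*

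**What the plan says.** All of this is in the protocol article, mainly section 17.1 (Statistical hypotheses).

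- **First level.** PAS is "converted to a trichotomized ordinal response of safe (PAS 1–3), penetration (PAS 4–5), or aspiration (PAS 6–8"), which gives three categories. If the PES patient does better, "then the treatment arm patient gets a score of +1 (winner) otherwise a score of −1 (loser) is assigned".
- **Second level.** A pair tied on PAS is compared "with respect to the second outcome (DOSS) and the same scoring procedure is followed". There is no third level. Section 11.3 describes DOSS as a seven-point scale.
- **Type of result.** For each pair, "a binary outcome is derived that indicates whether the treated patient or the control patient performs better".
- **Estimand and test.** P is introduced by the clause "If P is the probability that a randomly picked treatment arm patient performs better than a randomly picked control arm patient". On that definition the mean score is given the expectation 2(P − 0.5). The test sets P ≤ 0.5 against P > 0.5 ("The hypothesis of interest is a one-sided null"). Section 17.4 sets the one-sided level at 0.025.
- **Power.** Section 17.2 reports, from simulations, that "100 patients per arm will be required to achieve a power of at least 90" percent. It assumes 50% against 65% of patients reaching PAS 1–5 and a DOSS benefit of 0.7 points. It does not give the tie rule used in the simulations, the DOSS SD, the split between safe and penetration, or the PAS–DOSS correlation.

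**The concern.** Two coarse ordinal scales in sequence leave a residue of pairs that are equal on both. The printed rule has two values and an open-ended else-branch, so at the last level such a pair falls into −1. A pair in which neither patient did better is then booked as a loss for PES.

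This concerns the only primary test. If the rule is programmed as printed and the mean score is compared with zero, the test is not centred under no effect, and the reported effect is shifted down by the tie share. Section 15 lets the data monitoring committee recommend stopping for futility or re-estimating the sample size at the interim analysis. If those rules use this score against zero, the shift carries into them as well.

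**Working it through.** **1. Algebra.** Let w, l and t be the shares of pairs that PES wins, loses and ties on both levels, with w + l + t = 1. As printed, P = w.

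- Ties scored −1: E = w − (l + t) = 2w − 1 = 2(P − 0.5). The printed formula is exact for any t.
- Ties scored 0: E = w − l = 2(P − 0.5) + t. The printed formula is wrong by t.
- Identical arms: w = l = (1 − t)/2. Under the literal rule P is below 0.5 and E = −t.
- The literal E equals (w − l) − t, so P > 0.5 requires the net win difference to exceed the tie share. Example: w = 48%, l = 44.5%, t = 7.5%. PES wins more often than it loses (net +3.5 points), yet P = 0.48 lies inside the null.

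**2. Tie share by hand, no effect, PAS and DOSS independent.** Section 17.2 gives 50% aspiration in controls. Assume that the other 50% splits evenly between safe and penetration. PAS ties: 0.50² + 0.25² + 0.25² = 0.375. Assume DOSS is normal around 4 with SD 1.5, rounded and limited to 1–7: 0.186 of pairs tie. Double ties: 0.375 × 0.186 = 0.070. If all PAS 1–5 patients are safe: 0.500 × 0.186 = 0.093.

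**3. The plan's own figure.** The 90% cannot be reproduced from the stated inputs alone. For orientation, at 100 per arm and one-sided 0.025, PAS 50% against 65% alone gives 57% power. A DOSS difference of 0.7 alone gives 98%, 91% or 70% for SD 1.2, 1.5 or 2.0.

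The hierarchical score was therefore simulated with the stated effects. Assumptions: DOSS SD 1.2 to 2.0 before rounding, control DOSS centred at 3 or 4, safe share of PAS 1–5 from 50% to 100%, PAS–DOSS correlation 0 to 0.6, no interim adjustment. With double ties scored 0, power is 72% to 98%. At least 90% is therefore attainable, for example 90.4% with 70% safe, SD 1.2 and correlation 0.

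**4. No effect, mean score tested against zero (z test), control DOSS centre 4.**

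| Safe share | SD | Corr. | Tie share | Mean score, ties −1 | Type I error, ties 0 | Type I error, ties −1 |
|---|---|---|---|---|---|---|
| 50% | 2.0 | 0 | 5.7% | −0.055 | 3.15% | 0.50% |
| 50% | 1.5 | 0 | 7.0% | −0.072 | 2.35% | 0.15% |
| 100% | 1.5 | 0 | 9.3% | −0.093 | 2.55% | 0.15% |
| 100% | 1.5 | 0.6 | 10.6% | −0.105 | 3.15% | 0.05% |

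The tie shares agree with step 2, and the mean scores with −t up to simulation error.

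**5. Stated effect, mean score tested against zero.** With ties scored −1, power is 40% to 71%, which is 21 to 45 points below ties scored 0. Example (all responders safe, centre 4, SD 1.5, correlation 0.6): w = 0.576, l = 0.321, t = 0.103. The mean score is 0.255 with ties 0 and 0.576 − 0.424 = 0.152 with ties −1. Power is 88.9% against 45.7%.

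**6. Permutation reference instead of a fixed zero.** Re-randomising the labels recentres the null.

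| Safe share, SD, corr. | Ties 0 | Ties −1, permutation | Ties −1, fixed zero |
|---|---|---|---|
| 70%, 1.2, 0 | 91.5% | 91.3% | 60.8% |
| 100%, 1.5, 0.3 | 91.3% | 91.5% | 55.0% |
| 50%, 1.5, 0.3 | 79.8% | 79.8% | 51.2% |

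With no effect (100%, 1.5, 0.3), rejection is 2.7%, 2.8% and 0.2% respectively. The power loss therefore needs both conditions: ties scored −1 and a comparison with zero.

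**The case against.** The strongest reply is that the text does not say that double ties are losses. At the PAS level the else-branch cannot include ties, because the next sentence sends them to DOSS; there it in effect means worse. The same procedure at DOSS may then mean better or worse only, with a residual tie left open for the SAP that section 17.4 announces. This stands as a possible reading, so it is not established that the sponsor intends ties as losses. It does not clear the text. On that reading the primary statistic is undefined for these pairs, and the binary statement still leaves no place for them.

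A reader might also infer that the 90% power claim is broken. The documents do not support that: the tie rule of the simulations is unknown, 90% is reachable with ties scored 0, and a permutation reference keeps power nearly unchanged even with ties scored −1. The article does not say which reference distribution will be used. Section 17.2 also treats 200 patients as a minimum, with up to 360 evaluable.

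Nor does the expectation formula hold only in the absence of ties: it is exact when ties score −1 and fails when they score 0.

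Finally, on the literal reading the error is conservative and cannot create a false claim of benefit. That is correct, but a primary test that can miss a real benefit for a clerical reason is still worth correcting.

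**Conclusion.** The point holds as a defect in the stated rule, whichever way ties are read. With ties as −1, the null P ≤ 0.5 is not the hypothesis of no benefit. With ties as 0, the printed expectation and the binary statement are wrong, and P ≤ 0.5 does not mean no benefit unless P gives half weight to ties. With ties left open, the score is undefined for about 5% to 12% of pairs.

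The size is conditional. If the rule is applied as printed and the mean is tested against zero, type I error is about 0.05% to 0.5% instead of 2.5%, and power at 100 per arm is roughly 20 to 45 points lower. These figures rest on the assumed DOSS SD, PAS split and correlation, none of which the article gives. The algebra in step 1 needs no such assumptions. The stated 90% is neither confirmed nor refuted.

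**What to change.** In section 17.1, and in the SAP before the interim analysis:

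1. Score each pair +1 (PES better), −1 (control better) or 0 (tied on both PAS category and DOSS).
2. Define P as P(win) + 0.5 P(tie). Then 2(P − 0.5) = 2w + t − 1 = w − l, so the printed expectation is correct and P ≤ 0.5 means no benefit.
3. Replace the binary-outcome sentence with a win, loss or tie result.
4. Confirm that the sample-size simulations and any interim rules used this scoring, and give the DOSS SD and PAS split assumed. If they did not use it, restate the power.

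In the simulations with ties scored 0, type I error was about 2.2% to 3.2%, around the nominal 2.5%. The cost is wording and one line of code; no patients are added unless step 4 shows that the power has to be restated.

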### Sample size determination

17.2

Sample size calculations were carried out using simulations and are adjusted for interim analysis. Assuming that 50% of control patients will move from PAS score of 6–8 at baseline to a PAS score of 1–5 post-intervention and the corresponding number of patients in the PES treatment group is 65% (15% effect-size) and that the PES treatment group will benefit with a mean increase of 0.7 points on the DOSS score, 100 patients per arm will be required to achieve a power of at least 90%. Thus N_planned_ = 200 is the minimum sample size (unless the study is stopped early for futility at the only interim analysis). To allow for adaptations in design with respect to sample size and population enrichment, a maximum (evaluable) sample of N_max_ = 360 is pre-specified. To account for a 10% lost-to-follow-up, a maximum of 400 patients will be recruited.

### Population for analyses

17.3

The Intent to Treat (ITT) Population will consist of all patients that were randomised, irrespective of their protocol adherence and continued participation in the study.The Per Protocol (PP) Population will consist of all randomised patients who completed the full PES or Sham treatment regimen according to their randomisation assignment and for whom the composite primary endpoint data are available.The Safety Population will consist of all patients that were enrolled in the study and underwent the screening FEES with or without subsequent placement of the PES Catheter.

### Statistical analyses

17.4

Tabulations will be produced for appropriate demographic, baseline, effectiveness and safety parameters. For categorical variables, summary tabulations of the number and percentage within each category (with a category for missing data) of the parameter will be presented. For continuous variables, the mean, median, standard deviation, minimum and maximum values will be presented. Time to event data will be summarized using Kaplan–Meier methodology using 25th, 50th (median), and 75th percentiles with associated 2-sided 95% confidence intervals, as well as percent of censored observations. Formal statistical hypothesis testing will be conducted at the 1-sided, 0.025 level of significance. A Statistical Analysis Plan (SAP) will detail all statistical analyses planned for this study and will be established prior to the planned Interim Analysis.

## Discussion

18

This study evaluates the effectiveness of PES treatment in reducing severity of unsafe swallowing in recently extubated ICU patients with oropharyngeal dysphagia.

Post-extubation ICU-acquired dysphagia represents a major therapeutic challenge without evidence-based treatment.^[44]^ PES stimulates afferent sensory feedback for the responsible motor-cortex, activates cortico-bulbar pathways, and increases swallow-related neurotransmitter concentration, all contributing to improved swallowing.^[1,29–31]^ Safety data on the use of PES in acute stroke patients has been provided.^[35]^ The PHAST-TRAC study^[26]^ demonstrated that PES improved swallowing in dysphagic tracheotomized stroke patients, enabling earlier decannulation compared to controls. Moreover, pre-publication data from the PHADER registry^[45]^ showed improved swallowing and shorter length of hospital stay in 50 ICU patients with neurogenic dysphagia treated with PES. Therefore, previous trials have focused mainly on patients after stroke, with outcomes related to removal or avoidance of tracheostomy. In contrast, the present trial includes a general population of critically ill patients, and will answer whether PES reduces severity of unsafe swallowing. The strengths of this trail are its size, measurements of multiple dysphagia scores, and the inclusion of a general ICU population. The following limitations to this study seem apparent. First, although most dysphagia scales are validated, they may be considered somewhat subjective to interpretation, however, all investigators are trained on the correct interpretation prior to study start. Second, some of the exclusion criteria may theoretically overlap or could be perceived as not mutually exclusive. Third, inclusion of patients might be limited by the required expertise needed for FEES and PES, especially during weekends. Fourth, some could consider the fact that PhINEST is an industry-sponsored trial as a limitation, however, adequate blinding of the Sponsor (blinded) and all respective site staff (e.g., FEES and other assessment investigators (blinded) vs PES treaters (unblinded)) is ensured, and all authors of the paper will have full access to the data at the end of the trial.

In conclusion, this trial will answer the question, whether PES can reduce dysphagia severity in a general ICU population with oropharyngeal dysphagia after extubation.
